#### Economic evaluation

The economic evaluation compares differences in societal costs to differences in the number of limited activity days (CEA) and quality-adjusted life years (CUA). The analysis has a six-month time horizon, without discounting. Group averages are statistically compared using two-sided bootstrapping and net-benefit analyses are used to compare costs to patient outcome. Sensitivity analyses are performed on the perspective (societal versus healthcare perspective) and the applied utility measure (Dutch EQ5D, VAS).

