## Methods

### Study design

This study is a three-arm, cluster randomized trial with a cluster pre-randomisation design
[7] (Figure 
1). Because the implementation strategies are primarily targeted at general practices, randomisation will occur at practice level (CONSORT guidelines for cluster trials, Table 
1[27]). Prior to obtaining informed consent from GPs and patients, practices will be allocated to one of the strategies. Follow-up per practice is 12 months. At patient level, follow-up duration is six months. In the ES and IS strategies, individual patient outcomes will be evaluated at baseline (first visit of a patient to the general practice for instruction on IBSM), and three and six months after a patient’s start with IBSM. Individual patient outcomes in the MS strategy will be evaluated at six months (end-point evaluation) after a patient’s start with IBSM.

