#### Blinding and strategy allocation

General practices (*i.e.*, 2,300 patients per ‘standard practice’) will be the unit of randomisation. Practices will be stratified according the following characteristics: postal code (area) and practice size (practices with <4 GPs are defined as a small practice, practices with ≥4 GPs as a large practice). Prior to informed consent, practices will be randomized into one of the strategies (1:1:1 ratio), in order to assess the participation level of practices per strategy. Practices will receive a letter containing information on the allocated implementation strategy and an invitation to participate in the project.

Both practices and patients will be blinded to group allocation. Researchers will not be blinded for group allocation. Randomisation will be conducted by [name] using a computer-generated, permuted-block scheme. General practices will be invited until enough practices per strategy are participating. General practices will be enrolled by [name], [name], and [name]. Patients will be enrolled by general practices.

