**Quality of life/patient utilities**			
Asthma related quality of life (AQLQ)	A	A	A,N
Utilities: (EQ-5D)	X	X	A,N

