**Costs**			
Healthcare and other costs (CostQ)	X	X	X, N

A = all strategies; X = Intermediate and Extended strategy; N = non-participating practices.

Asthma control is using the 7-item Asthma Control Questionnaire (ACQ), the optimal cut-point for ‘controlled’ is ≤0.75 and a value of ≥1.50 confirms ‘not controlled’ asthma
[28]. Lung function will be measured as the Forced Expiratory Volume in one second (FEV_1_). Patients receive a handheld electronic spirometer (PiKo-1: Ferraris; Hertford, UK) and are instructed to report the highest value of three measurements in the morning before taking medication
[1]. The presence of exacerbations is assessed; they are defined as deterioration in asthma that required emergency treatment or hospitalization (collected by quarterly questionnaire) or the need for oral steroids for three days or more (collected by pharmacy records) or the need for oral steroids for asthma as judged by the attending physician.

Exacerbations are defined according to ATS/ERS statement
[40]:

Severe exacerbations require at least one of the following: systemic corticosteroids (tablets, suspension, or injection) usage or an increase from a stable maintenance dose, for three or more days; or a hospitalization or emergency room visit because requiring systemic corticosteroids.

Moderate exacerbations require ≥ 1 of the following features, lasting for two or more days: deterioration in symptoms, deterioration in lung function, and/or increased rescue bronchodilator use.”

Health education impact is assessed by the health education impact questionnaire (heiQ)
[41]. Self-reported medication adherence is measured by the Medication Adherence Report Scale
[32]. Illness perceptions are assessed by using the Brief Illness Perception Questionnaire (Brief IPQ)
[33]. In addition, asthma symptom utilities are obtained from the Asthma Quality of Life Questionaire (AQLQ)
[42], EQ-5D
[31,43] and a visual analogue scale (VAS).

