#### Analysis of clinical data

The number of patients with a clinically relevant improvement in asthma-related quality of life is based on a minimal clinical importance of difference (MCID) of 0.5 for the AQLQ
[30].Patient utilities: asthma symptom utilities are obtained from the AQLQ
[42]; indirect utilities from the general public are obtained using the EQ-5D
[31,43]. This allows the calculation of quality-adjusted life years (Qalys). In the base case analysis, Qalys are estimated using societal utilities obtained using the Dutch EQ-5D tariff
[45]. For sensitivity analyses, Qalys are estimated using a VAS (transformed using a power transformation). Data on healthcare provider utilization and other related costs provide input for calculation of the contract price that GPs will have to negotiate for this improved service. Ideally, this is in the form of a primary care diagnosis and treatment standard fee.

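### For ES versus IS, the planned comparison of average QALYs leaves out the baseline EQ-5D that both arms collect, so a baseline utility gap enters the incremental QALY and avoidable variance is kept

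*Protocol article*

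**What the plan says.** Three parts of the protocol article bear on this.

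- **Method.** The analysis subsection on economic evaluation states: "Group averages are statistically compared using two-sided bootstrapping and net-benefit analyses are used to compare costs to patient outcome". It adds: "The analysis has a six-month time horizon, without discounting". Its sensitivity analyses vary the cost perspective and the utility measure; none concerns baseline utility.
- **Utility.** Under Analysis of clinical data: "In the base case analysis, Qalys are estimated using societal utilities obtained using the Dutch EQ-5D tariff".
- **Schedule.** In Table 4 the row "Utilities: (EQ-5D)" carries the code X at 0 and 3 months and A,N at 6 months. The key reads: "A = all strategies; X = Intermediate and Extended strategy; N = non-participating practices". The Study design section agrees: "In the ES and IS strategies, individual patient outcomes will be evaluated at baseline", and again at three and six months. For MS it says: "Individual patient outcomes in the MS strategy will be evaluated at six months (end-point evaluation) after a patient’s start with IBSM".

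So ES and IS have all three EQ-5D readings and MS has one. The Endpoint evaluation section also limits IS and ES patients who decline the program to the six-month assessment.

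**The concern.** A six-month QALY built from EQ-5D at 0, 3 and 6 months contains the baseline value as one of its terms, and baseline also predicts the two later values. If the ES and IS groups start at different utilities, a plain difference in average QALYs counts part of that head start as a strategy effect, and the incremental net benefit inherits it.

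Some gap is to be expected. There are 14 practices per arm, stratified only by postal code and practice size. Recruitment may add to chance, since practices learn their strategy by letter before consenting and then "Patients will be enrolled by general practices".

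Even without a gap, leaving out a strong predictor that is already measured widens the interval. Cost-effectiveness is one of the four stated objectives. The Implications section asks whether continuing support adds value, and that question is the ES versus IS contrast.

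**Working it through.** **Inputs from the protocol.** EQ-5D at 0, 3 and 6 months in ES and IS (Study design, Table 4); six-month horizon; 14 practices of 10 patients per arm; ICC 0.25 (Sample size calculation). The protocol states no QALY effect, SD, correlation or power, so there is no QALY figure to reproduce. Its patient number does reproduce: 5% versus 30%, two-sided 0.05, 80% power, with continuity correction gives 43 per arm; the design effect is 1 + 9 × 0.25 = 3.25; 43 × 3.25 = 139.75, so 140 per arm.

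**Assumed.** Trapezoidal QALYs; equal SD at each visit; correlation rho between visits, either equal for all pairs or decaying with time (AR(1)); where an SD is needed, 0.2.

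**Weights.** Two intervals of 0.25 years give 0.125, 0.25 and 0.125 for months 0, 3 and 6.

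**Carry-over of a baseline gap d, equal correlation.**
- Baseline weight alone (rho = 0): 0.125d.
- With correlation: 0.125 + (0.25 + 0.125) × rho = 0.125 + 0.375 rho, times d.

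**Share of QALY variance explained by baseline, equal correlation.**
- Var(QALY)/SD² = (0.125² + 0.25² + 0.125²) + 2 rho (0.125×0.25 + 0.25×0.125 + 0.125×0.125) = 0.09375 + 0.15625 rho.
- R² = (0.125 + 0.375 rho)² / (0.09375 + 0.15625 rho).
- At rho 0.5: 0.3125² / 0.171875 = 0.0977 / 0.1719 = 0.57.

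| rho | carry-over (equal corr.) | R² equal corr. | R² AR(1) |
|---|---|---|---|
| 0.2 | 0.20d | 32% | 27% |
| 0.3 | 0.24d | 40% | 33% |
| 0.5 | 0.31d | 57% | 48% |
| 0.7 | 0.39d | 74% | 66% |
| 0.8 | 0.43d | 83% | 77% |

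R² passes one half only above rho 0.42 (equal correlation) or 0.52 (AR(1)).

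**How large a gap chance alone can give.** SE of the baseline difference = 0.2 × √[(2/140)(1 + 9 × ICC)], which is 0.029 at an ICC of 0.05 (assumed) and 0.043 at 0.25 (the protocol's value, set for participation and not for utility). A gap of 0.03 is therefore about one standard error or less. At rho 0.5 it adds 0.3125 × 0.03 = 0.009 QALY. A true gain g present at 3 and 6 months yields 0.375g, so the same 0.009 would look like a sustained utility gain of 0.009/0.375 ≈ 0.025.

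**Effect on the test.** Simulation with 14 practices of 10 per arm, rho 0.5, SD 0.2, all patients with baseline data, and a t test on practice means:
- True sustained gain 0.05, practice variation present at baseline too: power 33% unadjusted and 64% adjusted at ICC 0.05; 16% and 33% at ICC 0.25.
- Same gain, practice variation only after baseline: 34% and 51%; 20% and 22%.
- No true effect, baseline gap 0.03: false-positive rate 12% (ICC 0.05) or 8–9% (ICC 0.25) unadjusted, about 5% adjusted.

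**The case against.** **The method section does not say that the averages are unadjusted.** The net-benefit method is given only by citation, a condensed article may leave covariates to an analysis plan, and the general Analysis section describes a random-effects model for repeated measurements. This stands in part: a fuller plan may add the covariate. But the economic evaluation has its own stated method, that method read plainly compares averages, its listed sensitivity analyses do not touch baseline, and the random-effects description names no baseline term and does not expressly cover QALYs.

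**The hypothesised contrasts are out of reach.** Hypothesis 4 sets ES and IS against MS. A reader might infer that baseline adjustment would repair those comparisons as well. It would not: MS has no EQ-5D at 0 or 3 months, so there is neither a baseline to adjust for nor an area under the curve without an assumed starting value. Table 4 does mark the AQLQ for all strategies at 0 months, but Study design and Endpoint evaluation give MS patients a six-month assessment only. Until these are reconciled, AQLQ is not an available substitute, and the figures above would not carry over to another instrument. This objection stands in full and sets the scope of the point.

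**Recruitment bias is weakest where the fix works.** The Extended strategy section says that ES and IS share the same start-up phase, which includes patient recruitment. That stands. The allocation letter may still affect which practices join, but for ES versus IS the case rests mainly on chance imbalance.

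**The gain may be small.** SD, rho and the gap are all assumed. Ten per practice is the number invited, and decliners have no baseline, so the 14 × 10 simulation is optimistic about data. At the protocol's ICC, the least favourable case moves power only from 20% to 22%. QALYs are also not a primary outcome. This limits the weight of the point but does not remove it.

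**Conclusion.** The point holds for ES versus IS among patients with baseline EQ-5D. There, the stated comparison omits a predictor that is part of the outcome and is already collected. A baseline gap d adds 0.125d to the incremental QALY by construction, and about 0.24d to 0.39d at an assumed rho of 0.3 to 0.7. The QALY variance that adjustment could remove is roughly 27% to 83% for an assumed rho of 0.2 to 0.8, depending on the correlation structure. These figures rest on trapezoidal QALYs and equal SDs as well.

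Two stronger readings are not supported. That more than half of the variance is left in cannot be asserted, because it depends on a correlation the protocol does not give. That EQ-5D at baseline is available throughout and merely unused is wrong for MS and for IS and ES decliners. This is a worthwhile improvement to a secondary analysis and does not affect the primary outcomes.

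**What to change.** In the analysis subsection on economic evaluation:

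1. For ES versus IS participants with a baseline EQ-5D, regress each patient's six-month QALYs on strategy and baseline EQ-5D utility. Take the strategy coefficient as the incremental QALY, re-estimate it in every bootstrap sample, and carry it into the net-benefit analysis.
2. In the VAS sensitivity analysis, use baseline VAS in the same way. Table 4 does not list the VAS separately, so confirm that it is collected at 0 months.
3. State that this adjustment is not available for contrasts with MS, or for IS and ES patients who decline the program, because their only EQ-5D is at six months.
4. Reconcile Study design and Endpoint evaluation with Table 4, which marks the AQLQ for all strategies at 0 months, before using any baseline measure in contrasts with MS.

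The cost is a few sentences and one covariate in the bootstrap, with no new patients and no new data for ES versus IS. The estimate then describes participants with baseline data, so how it sits with the intention-to-treat statement needs to be spelled out. Participants who lack a baseline value need a stated imputation rule if they are to be kept in.

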#### Economic evaluation

The economic evaluation includes outcomes on cost-effectiveness and cost-utility. Medical costs, such as prescribed medication are assessed from electronic patient records (with written patient permission) complemented with the patient’s report on medication purchased elsewhere
[44]. In addition, actual treatment advice by the care provider and treatment advice by the system are registered. Healthcare consumption, absenteeism and productivity loss, and the number of limited activity days are measured by using the Cost Questionnaire
[34]. Furthermore, data on patient contacts (frequency of in-practice routine asthma consultations, telephone/email consultations, and unscheduled visits) are registered.

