#### Cost-effectiveness

Cost-effectiveness of treatment strategies is evaluated by incremental net-benefit analysis
[46]. Net health benefit addresses cost-effectiveness ratios by assuming values for the willingness to pay per unit of effectiveness. The cost analysis includes both medical (medication, visits, and hospitalizations) and non-medical costs (productivity losses, informal care). Other costs are estimated using quarterly cost questionnaires
[34] Costs are valued according to standard prices charges
[47] including time and travel costs.

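### The ES versus IS economic comparison names no use of the baseline Cost Questionnaire collected in both arms, so precision is lost and chance imbalance partly carries into the incremental estimates

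*Protocol article*

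**What the plan says.** The analysis section headed Economic evaluation sets societal costs against limited activity days and against quality-adjusted life years. On the horizon it says: "The analysis has a six-month time horizon, without discounting". On the comparison it says: "Group averages are statistically compared using two-sided bootstrapping and net-benefit analyses are used to compare costs to patient outcome". The sensitivity analyses listed there concern only the perspective and the utility measure. No baseline value appears in either place.

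The measurement section, also headed Economic evaluation, says: "Healthcare consumption, absenteeism and productivity loss, and the number of limited activity days are measured by using the Cost Questionnaire". Prescribed medication is taken from electronic patient records instead. The Cost-effectiveness section adds: "Other costs are estimated using quarterly cost questionnaires".

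In Table 4 the Cost Questionnaire row carries code X (IS and ES) at 0, 3 and 6 months, and code N (non-participating practices) at the end-point. Under Study design and Endpoint evaluation, MS patients, and IS or ES patients who decline the internet programme, are assessed at six months only.

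**The concern.** In IS and ES the effect measure of the cost-effectiveness analysis, and much of its cost side, has a baseline value. Prior cost and prior activity limitation usually predict later values. A comparison of group averages ignores this. Its intervals are then wider than the data require, and part of any baseline difference between the arms appears in the incremental cost, the incremental limited activity days and the net benefit.

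ES versus IS deserves this care. Under Extended strategy the two arms share the start-up phase and differ only in execution-phase support. Under Implications the authors ask whether start-up support is enough and whether continuing support adds value. Only this pair answers that. The sample size was set for participation, so nothing secures precision for the economic result.

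**Working it through.** **The plan's own figure.** No figure is given for the economic analysis. The sample size for participation reproduces: 5% versus 30% (an increase of 25 points), two-sided alpha 0.05, power 80% and continuity correction give 43 per arm. The design effect is 1 + (10 − 1) × 0.25 = 3.25, and 43 × 3.25 = 139.75, so 140 per arm in 14 practices of 10. This supplies the cluster numbers below. It says nothing about costs.

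**Assumptions, since the article gives no cost SD, correlation or ICC.**
- Each quarterly form covers the preceding quarter, so month 0 describes the quarter before the programme starts, and months 3 and 6 make up the six-month total.
- Quarterly values have equal SD s and equal correlation r.

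**Variance removed by the baseline form.**
- SD of the two-quarter total = s√(2 + 2r).
- Correlation of baseline with the total: ρ = 2r/√(2 + 2r).
- Share of variance removed = ρ². Interval width falls by 1 − √(1 − ρ²).
- A baseline gap of 0.2 SD carries 0.2ρ SD into the six-month difference.

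| r | ρ | variance removed | interval narrower by | carry-over of a 0.2 SD gap |
|---|---|---|---|---|
| 0.1 | 0.13 | 2% | 1% | 0.03 SD |
| 0.3 | 0.37 | 14% | 7% | 0.07 SD |
| 0.5 | 0.58 | 33% | 18% | 0.12 SD |
| 0.7 | 0.76 | 58% | 35% | 0.15 SD |

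**Allowing for patients without a baseline form.** The table credits every patient with one. Decliners have none, yet the Analysis section specifies intention-to-treat and the Discussion includes costs of non-participating patients. As a low case take 30% with a form, which is 5% + 25 points from the sample size section. That figure concerns frequent use, so it is only a proxy. If holders and non-holders have similar cost variance, the share removed is about 0.30ρ². For r = 0.3, 0.5 and 0.7 this is 0.30 × 14%, 33% and 58%, or about 4%, 10% and 17%. Intervals narrow by about 2%, 5% and 9%.

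**How likely is a chance gap?** The standard error of a baseline difference, in SD units, is √(2/n_eff), with n_eff = 140/(1 + 9 × ICC).
- ICC 0.05: n_eff = 140/1.45 = 96.6, SE = 0.144, and the probability of a gap of at least 0.2 SD is about 17%.
- ICC 0.25: n_eff = 140/3.25 = 43.1, SE = 0.215, and the probability is about 35%. This ICC was set for participation, so it only marks a high case for costs.

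**Which contrasts can be adjusted.** ES versus IS can. IS versus MS and ES versus MS cannot, because code X excludes MS. As coded, Table 4 shows no Cost Questionnaire at any time for participating MS practices.

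**The case against.** The strongest objection is that the article never calls the comparison raw or unadjusted. Net-benefit analysis can carry covariates, and an article commonly leaves covariates to an analysis plan. This stands in part: the absence of adjustment is an inference. But the article is not silent here. It states the comparison, lists the economic sensitivity analyses, and gives the baseline form no use. The random-effects model under Analysis is described for the process and effect evaluation and does not clearly cover costs.

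Second, hypothesis 4 sets ES and IS against MS, not against each other. That is right, and it limits the point to ES versus IS. A reader might infer that the whole cost-effectiveness analysis should be baseline-adjusted. The planned data do not allow it.

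Third, IS and ES recruit patients through the same start-up components, so differential selection is less plausible for this pair than against MS. The invitation letters describe different strategies, so some selection of practices remains possible. What is left is mainly chance, which a valid interval already reflects. A reader might infer that the unadjusted estimate is biased. The documents do not show that.

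Fourth, a reader might infer that the month-0 form would be added into the six-month total. Nothing in the article says so.

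Finally, medication cost comes from patient records, so the baseline form matches only part of total cost, and its correlation with that total may be lower than assumed. This stands.

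**Conclusion.** The point holds for ES versus IS only, as a loss of precision and an exposure to chance (possibly some selection) imbalance among few practices. It is not a demonstrated bias. With baseline forms for all patients, which is an upper bound, adjustment would remove about 14% to 58% of the variance at assumed quarterly correlations of 0.3 to 0.7. With forms for about 30%, it would remove about 4% to 17%. At a correlation of 0.1 the gain is negligible. The change is worth making because the data are already scheduled and the pair answers a question the authors pose. It does not repair the hypothesised contrasts with MS.

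**What to change.** In the analysis section on economic evaluation, state for ES versus IS that incremental cost, incremental limited activity days and net benefit come from a regression on strategy with the matching baseline Cost Questionnaire value as covariate. Run the model inside a bootstrap that respects practice clustering, for example by resampling whole practices. Report the unadjusted comparison alongside. State that IS versus MS and ES versus MS remain unadjusted because MS has no baseline form.

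Patients who decline the programme have no baseline form, and participation may itself depend on strategy. Fill the missing covariate by one rule common to both arms, such as the pooled mean, so that the intention-to-treat population is kept. Add a check restricted to patients with a baseline form. Neither is perfect: a common fill can shift the estimate if participation differs between IS and ES and participants differ in prior cost, and the restricted check conditions on something that happens after allocation. Reporting all three results makes this visible.

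The cost is analysis wording plus the missing-covariate rule. No new data collection is needed. Note in the text that the covariate does not cover prescribed medication taken from patient records.
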